## Methods

### Design

A nonrandomized pilot study design will be used with all participants receiving 16 weekly sessions of e-CBT. Functional magnetic resonance imaging (fMRI) will be conducted at baseline and posttreatment to evaluate activation level changes in the basal ganglia and frontal cortex. Clinically validated symptomology questionnaires will be used to evaluate treatment efficacy. In addition, qualitative interviews will be conducted to gather personal demographic information as well as information regarding participant experience while using the web-based psychotherapy clinic. The pilot study has been registered on the ClinicalTrials.gov Protocol Registration and Results System (NCT04630197). In addition, ethics approval has been obtained from the Queen’s University Health Sciences and Affiliated Teaching Hospitals Research Ethics Board (HSREB; file number 6031276).

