### Participants

Participants (n=10) will be recruited from family medicine and psychiatric clinics at Queen’s University and Kingston Health Sciences Centre sites (Hotel Dieu Hospital and Kingston General Hospital) in Kingston, Ontario, Canada. In addition, local and social media advertisements will be used. Participants will be enrolled in the study based on referrals from outpatient clinics and family doctors as well as self-referrals. Those invited and interested in participating will have the study protocol explained and an evaluation done by a psychiatrist on the research team through a secured video appointment. Participants will be evaluated for a diagnosis of OCD based on the *Diagnostic and Statistical Manual of Mental Disorders, 5th Edition* [44]. After a diagnosis of OCD is confirmed and the participant is given written and verbal instructions on how to participate in the study, informed consent will be obtained.

The inclusion criteria include the following: between the ages of 18 and 65 years at the start of the study, a diagnosis of OCD according to the *Diagnostic and Statistical Manual of Mental Disorders, 5th Edition* criteria, competence to consent to participate, ability to speak and read English, and consistent and reliable access to the internet. Exclusion criteria include the following: having any metal implants or additional factors deemed not safe for an MRI scan, active psychosis, acute mania, severe alcohol or substance use disorder, and/or active suicidal or homicidal ideation. In addition, if a participant is currently receiving another form of psychotherapy, they will be excluded from the study.

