### Outcomes

The primary outcome measure will be changes in activation levels of the basal ganglia and frontal cortex. This will be collected through detectable changes in BOLD values from the fMRI scans at baseline and after treatment (week 16). The secondary outcomes will be changes in symptom severity, quality of life, and functioning. Changes in symptom severity will be evaluated using clinical symptomatology questionnaires (Yale-Brown Obsessive-Compulsive Scale and Obsessive-Compulsive Inventory, Revised) [46,47]. Changes in quality of life will be measured using the Quality of Life and Enjoyment Questionnaire [48]. Changes in levels of functioning will be measured using the Sheehan Disability Scale [49]. All questionnaires will be collected directly through OPTT at baseline, after session 8, and after treatment (week 16).

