### Analysis

For the fMRI data (primary outcome), a 0.5% (eff=0.005) change in BOLD hemodynamic response function will be considered a detectable signal variation between conditions (*P*>10^-6^). An estimated paradigm of expected BOLD response will be created, and the correlation between the real and expected signals will be calculated to detect noise using a general linear model:

S = βX + e **(1)**

Where, S is the time-series data, β is the value for each pattern, X is the set of time-series patterns, and e is the residual.

The general linear model will provide a β value for each term in the basis set and a T value for each β. The BOLD contrast between conditions and scanning periods (ie, baseline and posttreatment) will be evaluated using one- and two-sample *t* tests, assuming a normal distribution. Realignment parameter regressors for the testing conditions will be implemented [56,57]. The effects at each condition will enter a group analysis using a random-effects model [58]. A group-level comparison will be used with small volume corrections performed for multiple comparisons using the Gaussian random field theory. Missing data points can be accounted for in the analysis with usable questionnaires and fMRI data using the linear model.

For questionnaire scores (secondary outcomes), a linear regression analysis will be used to identify variables associated with the outcome measures while controlling for demographic variables (ie, age, sex, and gender). Repeated measures of analysis of variance will be conducted to determine changes between periods (ie, baseline, week 8, and posttreatment) questionnaire scores. Greenhouse-Geisser adjustment for F-statistics and Bonferroni corrections for multiple comparisons will be used. Using the Pearson correlation coefficient, the correlation between the questionnaire score and the BOLD response will be evaluated. Data outliers will be defined as SD 3.29 away from the mean on scores.

Skew and kurtosis will be analyzed assuming a normal distribution in the questionnaire and fMRI data at all collection time points. Age, gender, and sex variables will be considered in knowledge creation and translation.

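### The secondary questionnaire regression names only age, sex and gender as adjustment variables, so a variable that merely tracks starting severity can look associated with outcome

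*Protocol article*

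**What the plan says.** The Analysis section of the protocol article describes the regression for the questionnaires in one sentence: "a linear regression analysis will be used to identify variables associated with the outcome measures while controlling for demographic variables (ie, age, sex, and gender". The candidate variables are not listed. The same section tests mean change separately: "Repeated measures of analysis of variance will be conducted to determine changes between periods (ie, baseline, week 8, and posttreatment) questionnaire scores".

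The Outcomes section shows that the baseline values will exist: "All questionnaires will be collected directly through OPTT at baseline, after session 8, and after treatment (week 16". It defines the outcomes as changes: "The secondary outcomes will be changes in symptom severity, quality of life, and functioning". The Analysis section, by contrast, calls the questionnaire scores themselves the secondary outcomes. Whether the regression's dependent variable is the week-16 score or the change is therefore not settled.

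The study has a single arm ("A nonrandomized pilot study design will be used with all participants receiving 16 weekly sessions of e-CBT") and is small ("Participants (n=10) will be recruited from family medicine and psychiatric clinics").

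**The concern.** A questionnaire's baseline score is usually related both to its later score and to its change. If the model does not hold it constant, any candidate correlated with starting severity inherits part of that relation, even if it carries no information about outcome once baseline is known.

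The direction of the artefact depends on the coding. On a scale where higher is worse, such a candidate would look like a marker of a poor final score in one coding and of a larger improvement in the other. Because the article does not fix the coding, the same irrelevant variable could be reported either way. At stake is how the exploratory associations are read, and whether they are carried into the expanded randomized trial that the Results section mentions.

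**Working it through.** **Inputs from the protocol article.** n = 10 (Participants); one arm (Design); adjustment for age, sex and gender (Analysis); questionnaires at baseline, after session 8 and at week 16 (Outcomes). The article gives no figure for this regression, so there is nothing to reproduce.

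**Assumed, because the documents give no values.** r = correlation of baseline with week-16 score, 0.3 to 0.7. rho = correlation of the candidate X with baseline, 0.3 to 0.7, with 0 as a reference. Two-sided 5% test. X has no effect given baseline.

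**Expected false coefficient.** Let baseline B and candidate X be standardised, and week-16 score Y = rB + error. Then:

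- week-16 score: cov(X, Y) = r × rho
- change: cov(X, Y − B) = −(1 − r) × rho

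At r = rho = 0.5 these are 0.5 × 0.5 = +0.25 and −(1 − 0.5) × 0.5 = −0.25 SD per SD of X.

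**Residual degrees of freedom.** Intercept, X, age and sex leave 10 − 4 = 6. A distinct gender term leaves 5. Adding baseline gives 5 or 4.

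**Simulated size at n = 10** (ordinary least squares; 4,000 runs per setting; age, sex and a near-duplicate gender term in the model):

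| r | rho | Mean coefficient, score / change | Rejection without baseline, score / change | Rejection with baseline | CI half-width for score, without → with baseline |
|---|---|---|---|---|---|
| 0.3 | 0.3 | 0.11 / −0.21 | 5.5% / 6.2% | 5.0% | 1.05 → 1.24 |
| 0.5 | 0.3 | 0.14 / −0.15 | 6.4% / 6.2% | 4.7% | 1.04 → 1.11 |
| 0.7 | 0.3 | 0.21 / −0.11 | 7.4% / 6.2% | 4.9% | 1.02 → 0.92 |
| 0.3 | 0.5 | 0.16 / −0.36 | 5.9% / 9.4% | 5.2% | 1.03 → 1.35 |
| 0.5 | 0.5 | 0.26 / −0.25 | 8.2% / 7.9% | 5.0% | 0.99 → 1.22 |
| 0.7 | 0.5 | 0.35 / −0.14 | 10.7% / 6.6% | 4.9% | 0.98 → 1.01 |
| 0.3 | 0.7 | 0.21 / −0.50 | 7.0% / 15.7% | 5.6% | 1.02 → 1.65 |
| 0.5 | 0.7 | 0.35 / −0.36 | 11.7% / 11.4% | 4.6% | 0.98 → 1.50 |
| 0.7 | 0.7 | 0.49 / −0.21 | 20.7% / 8.7% | 4.6% | 0.91 → 1.22 |

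With only age and sex in the model, the worst case for the score (r = rho = 0.7) is 24.2%. A separate simulation with age and sex (6,000 replicates) gives 9.5% for the score and 9.6% for the change at r = rho = 0.5. At rho = 0 the rate stays near 5%. At n = 100 and r = rho = 0.5 it would be about 71%: the bias does not shrink with sample size, and at n = 10 low power masks it.

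**Precision.** For a candidate unrelated to baseline and the week-16 score as outcome, the ratio of CI half-widths (with / without baseline) is √(1 − r²) × √(df/(df − 1)) × t(df − 1)/t(df). At r = 0.5 and df = 6: 0.866 × 1.095 × (2.571/2.447) = 0.997. At df = 5: 0.866 × 1.118 × (2.776/2.571) = 1.046. At r = 0.3 the ratios are 1.10 and 1.15; at r = 0.7 they are 0.82 and 0.86. For candidates that do track baseline, the table shows a wider interval for the score in eight of nine settings.

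**Score versus change.** If Y = a + βX + γB, then Y − B = a + βX + (γ − 1)B. With baseline in the model, β is the same for both outcomes.

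**The case against.** The abbreviation before the three covariates closes the list of demographics, not of all model terms. The candidates are unlisted, so a baseline score could be among them, and a condensed article may leave fuller detail elsewhere. It is true that the text does not rule baseline out. But it does state an adjustment set, and nothing in it holds baseline constant while another variable is tested.

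A reader might infer that omitting baseline also throws away precision. The documents do not support that at n = 10: the lost degree of freedom and the overlap between candidate and baseline usually offset or outweigh the smaller residual variance. In a power simulation at r = 0.5, adding baseline to age and sex moved power only from 54% to 55%.

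A reader might also want baseline to replace a demographic. The simulated gain from doing so, 54% to 64% at r = 0.5, comes from dropping sex where sex was given no effect on outcome. A gender term that coincides with sex is aliased and frees no degree of freedom. The Analysis section also commits to considering age, gender and sex when reporting, which a swap would cut against.

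Nor is this regression the plan's only look at associations. Pearson correlations link questionnaire scores to the BOLD response, and repeated-measures analysis of variance tests mean change. No efficacy estimate rests on the regression. Finally, baseline adjustment removes the bias fully only if the measured score captures the severity that the candidate tracks; with a noisy questionnaire some confounding remains. All of this limits the point without removing it.

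**Conclusion.** The point holds as one about confounding by starting severity. With the stated adjustment set, a variable that has no relation to outcome given baseline gets a false coefficient of r × rho on the week-16 score and −(1 − r) × rho on the change. At assumed correlations of 0.5 the nominal 5% test rejects in about 8% to 10% of cases; over 0.3 to 0.7 the range is about 5.5% to 24%, the top of it for the week-16 score. Including baseline brings the rate to about 5%.

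These sizes rest on assumed correlations and on a candidate that tracks baseline; for one unrelated to baseline there is no inflation. It is a cheap improvement to an exploratory secondary analysis. It does not touch the primary fMRI outcome or the test of mean change, and it carries no claim of lost precision.

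**What to change.** In the Analysis section, state that for each questionnaire the week-16 score is regressed on the candidate variable with that questionnaire's own baseline score as a covariate, alongside the planned demographics. Enter sex and gender together only if they are distinguishable in the sample. Label the results exploratory associations, because a single arm of 10 cannot separate treatment response from general prognosis even after adjustment.

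The change takes about two sentences and needs no new data. It costs one residual degree of freedom (6 to 5, or 5 to 4 with a distinct gender term) and, at this sample size, intervals that are often somewhat wider. In return, the coefficients are no longer confounded by measured starting severity, and the choice between score and change no longer affects them.

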**Methods:**

Individuals with OCD will be offered a 16-week e-CBT program with exposure and response prevention mirroring in-person CBT content and administered through a secure web-based platform. The efficacy of the treatment will be evaluated using clinically validated symptomology questionnaires at baseline, at week 8, and after treatment (week 16). Using functional MRI at baseline and after treatment, brain activation levels will be assessed in the resting state and while exposed to anxiety-inducing images (eg, dirty dishes if cleanliness is an obsession). The effects of treatment on brain activation levels and the correlation between symptom changes and activation levels will be analyzed.

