### Therapy

Weekly sessions of e-CBT will be conducted through the Online Psychotherapy Tool (OPTT; OPTT Inc), a secure, web- and cloud-based mental health care delivery platform. These web-based sessions will consist of approximately 30 slides and interactive therapist videos, with 16 modules in total (1 module per week). The content and format of these web-based sessions will mirror in-person CBT for OCD. The connection between thoughts, behaviors, emotions, physical reactions, and the environment will be a focus. Moreover, mindfulness, body scanning, self-care, goal setting, thinking errors, the 5-part model, and thought records will be employed as techniques for participants. ERP will be incorporated into the e-CBT program as this is the first-line route of treatment. Slides will highlight different topics each week and include general information, an overview of skills, and homework on that topic. The homework included in each session will be submitted through OPTT and reviewed by therapists, with personalized feedback provided within 3 days of submission. Weekly homework submission for feedback will be mandatory before being eligible for the next session. After each completion of the e-CBT program, participants will be interviewed to investigate their experience using OPTT and their perceptions of how the treatment went. OPTT can be accessed from a variety of devices (ie, desktop computers, laptops, cell phones, and tablets) and internet browsers.

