### Compliance

As with all mental health disorders, treatment compliance is always an area of focus when designing interventions. Participants will have the importance of treatment compliance explained to them during the informed consent process, and participants will need to submit their homework assignments through OPTT before gaining access to their next treatment session. From a previous meta-analysis conducted, the estimated completion rate from in-person psychotherapy is approximately 75% [50]. Additional meta-analyses found treatment adherence for web-based psychotherapy to be between 61% and 66%, with no significant difference with in-person psychotherapy [51-53]. A study investigating the efficacy of a 10-session e-CBT program for OCD had a mean completion of 7.28 sessions [54]. Previous research using OPTT indicated participants completed >8 sessions on average, with over half the participants completing all sessions. In a previous project using e-CBT for patients with generalized anxiety disorder, 90% of participants completed 10-12 weeks of the 12-week program, with over 75% of participants being retained for a 12-month follow-up [55].

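### The repeated-measures ANOVA for the questionnaires does not fit the plan's own missing-data statement, and the midpoint is defined both as week 8 and as session 8

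*Protocol article*

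**What the plan says.** All references are to the protocol article.

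- **Analysis, on change in questionnaire scores:** "Repeated measures of analysis of variance will be conducted to determine changes between periods". The periods are baseline, week 8 and posttreatment, with a Greenhouse-Geisser adjustment and Bonferroni corrections.
- **Analysis, on missing data** (at the end of the fMRI paragraph): "Missing data points can be accounted for in the analysis with usable questionnaires and fMRI data using the linear model".
- **Abstract, Methods, on timing:** "clinically validated symptomology questionnaires at baseline, at week 8, and after treatment (week 16").
- **Outcomes, on timing:** all questionnaires are collected through the online platform "at baseline, after session 8, and after treatment (week 16").
- **Therapy and Compliance:** there is one module per week, and the next one opens only once the homework for the current one has been submitted.
- **Therapy, on user experience:** "After each completion of the e-CBT program, participants will be interviewed to investigate their experience using OPTT". The Design section also announces interviews, without giving their timing or saying who is eligible.
- **Participants, on size:** "Participants (n=10) will be recruited from family medicine and psychiatric clinics".
- **Compliance, on expected adherence:** several earlier figures are cited and none is adopted for this trial.

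**The concern.** A classical repeated-measures ANOVA needs a complete row for each participant. Someone with a baseline and a midpoint but no posttreatment score contributes nothing, nor does someone who missed only the midpoint. The plan nevertheless says that missing points can be accounted for, so the named method and the stated intention do not fit each other.

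The two definitions of the midpoint make this worse. A visit tied to session 8 comes late for anyone who falls behind and never comes for anyone who stops earlier. A late score would still be analysed as week 8, and an absent one would remove the participant from the ANOVA altogether.

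At stake are the secondary efficacy results and the feasibility and user-experience question listed under Objectives. The Results section says that a randomized trial is planned after this pilot. If the people who stop are those who benefit less, a completers' estimate passed on to that trial would look too good.

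**Working it through.** **1. Does any named method use an incomplete participant?** The missing-data sentence refers to the linear model. The models named before it in that section are the general linear model for the BOLD time series and the random-effects group model for fMRI. For the questionnaires the section names linear regression, repeated-measures ANOVA and the Pearson correlation. In standard form, none of these recovers a participant's missing score. The sentence therefore has no questionnaire model that would carry it out.

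**2. How far apart are week 8 and session 8?** If a module takes *d* days, session 8 ends 8*d*/7 weeks after the start. At *d* = 7, the nominal pace, this is week 8. Each extra day per module moves the midpoint by 8/7 = 1.1 weeks. The article gives no expected pace, so the size of the delay is unknown.

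**3. How likely are incomplete data?** There is no sample-size calculation or drop-out allowance to reproduce; n = 10 is simply stated. The rates come from Compliance: "treatment adherence for web-based psychotherapy to be between 61% and 66"%, "the estimated completion rate from in-person psychotherapy is approximately 75"%, over half completing all sessions in earlier work on this platform, and 90% completing 10–12 of 12 weeks in an anxiety project. Treating each rate *p* as the chance that a participant completes, independently of the others:

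| Source | *p* | Expected completers, 10*p* | Chance all 10 complete, *p*^10 |
|---|---|---|---|
| Same platform (over half; lower limit) | 0.50 | 5.0 | 0.1% |
| Web-based, low | 0.61 | 6.1 | 0.7% |
| Web-based, high | 0.66 | 6.6 | 1.6% |
| In-person | 0.75 | 7.5 | 5.6% |
| Anxiety project | 0.90 | 9.0 | 34.9% |

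The number itself is uncertain. At 61% and 66%, the binomial chance of exactly 6 or 7 completers is 47% and 49%, and the chance of 5 or fewer is 34% and 23%. The cited mean of 7.28 out of 10 sessions in an e-CBT program for OCD is a mean number of sessions, not a completion rate, so it is left out.

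**4. How large could the bias be?** The documents do not say how drop-out relates to response, so this is an illustration on assumed inputs: true Y-BOCS changes of −4 (week 8) and −8 (week 16), SD 5.5, correlation 0.5, 63% retained, and drop-out after week 8 depending on the midpoint change through a logistic slope. With these inputs the SD of change is 5.5 × √(2 × (1 − 0.5)) = 5.5, and the shift at week 16 is half the shift at week 8. The table gives the expected completers' mean change.

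| Slope per point | Retention, 5 points better vs 5 points worse than average | Week 8 (true −4) | Week 16 (true −8) |
|---|---|---|---|
| 0 | 63% vs 63% | −4.00 | −8.00 |
| 0.05 | 69% vs 57% | −4.55 | −8.28 |
| 0.3 | 91% vs 33% | −6.29 | −9.15 |

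The direction follows from the assumption that poor responders leave. The size runs from nothing to about 2.3 points at week 8, and nothing in the article picks out a row.

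**The case against.** **Adherence is not questionnaire availability.** This stands. The final assessment is labelled week 16 and the Imaging section places the scan after week 16. Neither section says that a participant who is behind or has stopped goes unassessed. A reader might infer that all follow-up depends on session progress, but only the midpoint is explicitly tied to a session.

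**The 61–66% range is one of several.** This also stands. A reader might conclude that the plan's own figures put the results on 6–7 completers. The Compliance section commits to no rate, and the full set gives about 5–9.

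**Dropping incomplete participants is not a stated rule.** Correct: it follows from the standard form of the named method. The linear-model sentence may be meant as a model-based fit, and details of missing-data handling may be in a document not shown. But the article does name the method, and that method in standard form cannot do what the sentence promises. The mismatch needs resolving even if the intention is sound.

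**The interviews are not restricted to completers.** The Therapy section places them after completion but does not exclude others, and the Design section sets no restriction. Non-completion is itself feasibility information that the platform records. It cannot be said that those who stop vanish from the feasibility result; the article simply does not say that they will be interviewed.

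**Favourable bias is not demonstrated.** It is conditional. It disappears if drop-out is unrelated to response, and the illustration covers Y-BOCS only. It also assumes that week 8 was observed, so it does not represent people who stop before the midpoint.

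**Conclusion.** The point holds in a limited form. The named ANOVA does not fit the missing-data statement, and the session-8 and week-8 definitions of the midpoint must be reconciled. Some incomplete data should be expected: even at the most favourable rate cited, all 10 complete only about 35% of the time, and at the web-based rates about 1% of the time. Expected completers are about 6–7 at the web-based rates and about 5–9 across all cited rates. These figures assume independent participants and take treatment completion as a stand-in for questionnaire completion.

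If poor responders leave more often, a complete-case estimate leans towards those doing well. The size cannot be derived from the article and may be zero. The loss of scores already collected does not depend on that assumption, and with 10 participants each lost row matters. The matter concerns secondary outcomes and the user-experience question, not the primary fMRI outcome. It is worth correcting but does not threaten the study as a whole.

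**What to change.** 1. In Analysis, replace the repeated-measures ANOVA with a linear mixed model for each questionnaire: time as a three-level factor, a participant random intercept, REML, small-sample degrees of freedom, and every available score included. Tie the missing-data sentence for questionnaires to this model.
2. Collect the questionnaires at calendar weeks 8 and 16 from baseline for everyone, whatever the number of sessions completed. Use week 8 throughout, including in Outcomes.
3. State that the week-16 questionnaires and the user-experience interview are also offered to participants who stop the program early.

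**Cost.** The first change is wording and standard software. The others need a few extra reminders and interviews. Estimates may look less favourable.

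**Limits.** A random intercept assumes equal correlation between visits, and a model on 10 people may give convergence or boundary warnings. The mixed model relies on missingness being explained by the observed scores. It does not repair drop-out that depends on unobserved ones, which is why collecting scores from those who stop matters as much as the change of model.

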### Objectives

This study will use a 16-week e-CBT with an ERP program to evaluate the effects of treatment on activation levels in the basal ganglia and frontal cortex. Previous findings suggest that CBT may partially reduce the hyperactivation commonly observed in OCD. It is hypothesized that successful treatment will decrease activation levels in the basal ganglia and frontal cortex when comparing pre- and posttreatment levels in patients with OCD with controls. This study will aim to address the following questions:

Does successful treatment result in changes in brain activation levels in regions involved in neural anxiety processing at the core of OCD pathology?Is there a correlation between changes in symptom severity and changes in brain activation levels after treatment in patients with OCD?What is the efficacy of this e-CBT program compared with control in improving symptoms, quality of life, and levels of functioning in patients with OCD?What is the feasibility and user experience of this e-CBT program from a patient perspective?

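### If Bonferroni is meant for the three period pairs of a questionnaire, a gating F test with unadjusted pairs would hold about 5% error with more power

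*Protocol article*

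**What the plan says.** The Analysis section of the protocol article states: "Repeated measures of analysis of variance will be conducted to determine changes between periods (ie, baseline, week 8, and posttreatment) questionnaire scores". The next sentence adds: "Greenhouse-Geisser adjustment for F-statistics and Bonferroni corrections for multiple comparisons will be used".

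The Outcomes section names four questionnaires, all secondary outcomes:
- two for symptoms ("Yale-Brown Obsessive-Compulsive Scale and Obsessive-Compulsive Inventory, Revised");
- one for quality of life ("Changes in quality of life will be measured using the Quality of Life and Enjoyment Questionnaire");
- one for functioning ("Changes in levels of functioning will be measured using the Sheehan Disability Scale").

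The study has one group ("A nonrandomized pilot study design will be used with all participants receiving 16 weekly sessions of e-CBT") and a planned size of ten ("Participants (n=10) will be recruited from family medicine and psychiatric clinics"), so every comparison between periods is within person.

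The article gives no significance level, expected change, standard deviation, within-person correlation or power for the questionnaires. It does not say whether pairwise tests depend on a significant F, or which comparisons Bonferroni covers.

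**The concern.** Three periods are a special case. After a significant overall F test the three pairwise comparisons need no further adjustment to hold the family-wise error. Dividing alpha by three as well moves the test of baseline against week 16 from 0.05 to 0.0167. With at most ten people, that makes a real change in symptoms, quality of life or functioning more likely to be reported as not shown. Because neither gate nor family is fixed, the sentence also covers procedures with quite different thresholds: 0.05/3, 0.05/4 or 0.05/12.

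**Working it through.** **Inputs from the protocol.** n = 10 in one group (Participants, Design). Three periods (Analysis), so 3 × 2 / 2 = 3 pairs. Four questionnaires (Outcomes), so 4 × 3 = 12 pairwise tests in all.

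**Assumptions, because the protocol gives no values.** Two-sided alpha 0.05 and normal scores. d, the mean change from baseline to week 16 divided by the SD of that change, is 0.8, 1.0 or 1.2. Correlations between periods are equal, or decay with time (0.5 or 0.7 between adjacent visits). The week-8 mean is at the baseline level, halfway, or at the final level. The protocol has no power figure of its own to reproduce.

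**Step 1: why the gate suffices.** Either all three means are equal, and any false pairwise claim first needs a false rejection by F, with probability about 0.05; or at most one pair is equal, so one true null remains, tested once at 0.05. This is closed testing with three hypotheses.

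**Step 2: error within one questionnaire, simulated.**
- F gate, pairs at 0.05: 3.5-5.3% over the full and partial nulls and the covariance patterns tried, including n = 6 and n = 10. The values just above 5% reflect simulation noise and the approximate Greenhouse-Geisser adjustment.
- F gate, pairs at 0.05/3: 1.6-2.7%.
- No gate, all means equal: 11-13% for unadjusted pairs, 3.8-4.7% with Bonferroni.

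**Step 3: power of one paired t test, n = 10.** Power = P(|T| > critical t), where T is noncentral t with 9 df and noncentrality d√10.

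| Level | Critical t | d = 0.8 | d = 1.0 | d = 1.2 |
|---|---|---|---|---|
| 0.05 | 2.26 | 62% | 80% | 92% |
| 0.05/3 | 2.93 | 40% | 60% | 78% |
| 0.05/12 | 3.81 | 19% | 35% | 53% |

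**Step 4: power of the whole procedure for baseline against week 16, n = 10.** Simulated with 200,000 replicates per case; ranges run over the correlation and week-8 patterns.

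| d | Bonferroni after F gate | Bonferroni, no gate | Holm, no gate | F gate, pairs at 0.05 |
|---|---|---|---|---|
| 0.8 | 36-40% | 40% | 41-46% | 47-61% |
| 1.0 | 57-60% | 60% | 62-67% | 69-80% |
| 1.2 | 76-78% | 78% | 80-84% | 86-92% |

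The last column exceeds both Bonferroni columns in every case, by about 7 to 21 points over ungated Bonferroni. With n = 8 (a sensitivity value, not a planned figure) and d = 1.0, Bonferroni gives 40-45% and the gated rule 54-67%.

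**Step 5: error across the four questionnaires, treated as independent.** At 5% each: 1 − 0.95⁴ = 18.5%. With gated Bonferroni at 1.7% to 2.7% each: 1 − 0.983⁴ = 6.6% to 1 − 0.973⁴ = 10.4%. A within-questionnaire F test gives no protection at this level.

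**The case against.** The strongest reply is that the protocol never states an F gate. Without one, Bonferroni is the error control: it brings 11-13% down to under 5%. A reader might infer that Bonferroni here is a redundant second correction with no error-rate benefit. The text does not support that, since the gate is not in it, and even with a gate Bonferroni lowers the actual error to about 2%. What remains is a comparison of procedures: adding a gate and dropping Bonferroni has more power than Bonferroni with or without a gate, at the same nominal 5% per questionnaire.

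Second, the family may be the four questionnaires. Bonferroni would then address a multiplicity that F does not touch. That stands, and it limits the point to the three-pair reading; for the other readings only the change to Holm applies.

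Third, the power figures rest on an assumed effect size, alpha and correlation. That stands too, so they are given as ranges. The direction did not change in any case tried.

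Fourth, a reader might infer that this lost power weakens the answer to the third study question. It does not. That question asks about efficacy against a control "in improving symptoms, quality of life, and levels of functioning in patients with OCD", and a single-arm change over time cannot answer it at any significance level.

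Finally, Bonferroni is a legitimate conservative choice for secondary outcomes in a pilot, and it gives simultaneous confidence intervals, which the gated tests do not. An article may also leave the gate and family to a fuller plan. Both are reasons to treat this as an improvement only.

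**Conclusion.** The point holds as an efficiency improvement. If the Bonferroni family is the three period pairs, the correction is valid but costs power that need not be lost to hold about 5% within a questionnaire. At n = 10 and d = 1.0 the choice is between 57-60% and 69-80% power for the change from baseline to week 16; over d = 0.8 to 1.2 the gated rule is better throughout. The closed-testing argument depends on there being exactly three periods. The size of the gain depends on the assumed alpha, effect and correlation. Nothing in the plan is invalid here, and the gain concerns secondary within-group change only.

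**What to change.** Replace the Bonferroni wording in the Analysis section with a rule such as: within each questionnaire, the Greenhouse-Geisser-adjusted F test for period is the gate; if it is significant at 0.05, the three paired comparisons are each tested at 0.05 without further correction; if it is not, no pairwise difference is claimed. State the level, since none is given now.

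If no gate is wanted, use Holm over the three pairs; it controls the same error and never rejects less than Bonferroni.

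If error is to be controlled across the four questionnaires, name the family and use Holm there as well. Holm over the four F tests protects claims that a questionnaire changed over time. If every pairwise claim must be covered jointly, apply Holm to all twelve comparisons.

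The cost is a sentence or two, with no new data or participants. Two downsides should be accepted openly. The gated tests give no simultaneous confidence intervals. Actual error also rises from about 2% (gated Bonferroni) towards 5% per questionnaire, so without a Holm step it can reach about 18.5% across four independent questionnaires.
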